## Abstract

**Background:**

HIV persists as a public health emergency in South Africa, especially among women of childbearing age. In response to the HIV epidemic, the Joint United Nations Programme on HIV/AIDS has put forth the 90–90-90 global goals to achieve an AIDS-free generation by 2020. This goal aspires to have 90% of people living with HIV diagnosed; 90% of those who test positive on sustained antiretroviral therapy (ART); and 90% of those on ART be virally suppressed. Ensuring access to ART is an important first step in reducing HIV incidence, especially among vulnerable populations such as women who use substances and bear the burden of HIV in South Africa. Additionally, alcohol and other drug (AOD) use and exposure to gender-based violence are associated with increased risk of HIV infection and reduced adherence to ART. However, no research has estimated ART adherence rates for women who use substances in South Africa since the government approved the provision of ART to all people living with HIV.

**Methods:**

The Women’s Health CoOp (WHC) is an evidence-based, woman-focused, behavioral intervention that addresses the intersecting risks of AODs, sex behaviors, and violence and victimization, with the primary goal of increasing skills and knowledge to reduce substance abuse and HIV risks and to improve ART adherence. The WHC has been packaged for further dissemination. This article describes the study protocol used to assess the feasibility and acceptability of implementing the WHC intervention into standard of care in Cape Town health clinics and substance abuse rehabilitation centers to reduce HIV risk behavior and increase ART adherence among women who use substances and are living with HIV.

**Discussion:**

Because few of the interventions that demonstrate efficacy for HIV prevention and ART adherence in randomized trials are sustainable, studies to adapt and test intervention variations are needed to determine the best strategies for implementing them in real-world, high-risk settings. However, implementation in real-world settings presents challenges. Consequently, intervention developers should consider the strengths and limitations of their anticipated implementation setting by engaging with key stakeholders before, during, and after the adaptation and implementation process when developing and attempting to scale-up interventions.

**Trial registration:**

NCT 02733003 and date approved 1/21/2016.

## Background

Mounting evidence indicates that large-scale provision of antiretroviral therapy (ART) is key to arresting the HIV epidemic [1]. Two key studies have demonstrated a decreased incidence of HIV among seronegative partners when their HIV-positive partners initiate ART as soon as they receive their diagnosis [2], and lower HIV prevalence among persons living in areas where there is greater ART use among people who are HIV-positive [1]. In light of the rigorous trials highlighting the overwhelming need to extend distribution of ART, in 2015 the World Health Organization revised its HIV treatment guidelines, recommending that all people living with HIV receive ART regardless of CD4 count [3]. Also, the Joint United Nations Programme on HIV/AIDS (UNAIDS) has put forth the 90–90-90 global goals to achieve an AIDS-free generation by 2020 [4]. This goal states that 90% of people living with HIV are diagnosed, 90% of those who test positive for HIV are on sustained ART, and 90% of those on ART will be virally suppressed [4].

Ensuring access to ART is an important first step in reducing HIV incidence. However, numerous barriers exist between access to ART and actual use and adherence. These barriers often relate to behavioral factors that increase a person’s risk of HIV acquisition or reduce their agency to access or adhere to their medications. In particular, previous research demonstrates that transactional sex, alcohol and other drug (AOD) use, and exposure to gender-based violence (GBV) are associated with increased risk of HIV infection and reduced ART adherence [5–12]. To curb the incidence of HIV and ensure that people living with HIV are able to live longer and healthier lives, it is important to implement evidence-based interventions (EBIs) that address gender context and reduce risk behaviors to help improve ART uptake and adherence. Implementation science provides a framework for determining the best strategies for integrating EBIs into standard healthcare practice and assessing their feasibility, acceptability, and effectiveness as they are rolled out in real-world settings [13].

In this article, we describe the protocol for a study funded by the U.S. National Institute on Alcohol Abuse and Alcoholism to assess the feasibility and acceptability of implementing an evidence-based, gender-focused intervention—the Women’s Health CoOp (WHC) program—in government health clinics that provide HIV testing and counseling (HTC), ART, tuberculosis (TB) treatment, and antenatal care; and in substance use rehabilitation (rehab) centers in South Africa. The project also assesses the effectiveness of the WHC among the women participants and the sustainability of the program in these settings over time.

### A focus on women and the 90–90-90 goal in South Africa

South Africa is the epicenter of the HIV epidemic; evidenced by the fact that 1% of the world’s population lives in South Africa, but about 17% of all persons living with HIV (5.6 million people) reside there [14]. Extremely vulnerable, impoverished women living in South African disadvantaged communities face myriad risks for HIV. For example, historically South Africa has had a patriarchal culture that fueled women’s social, legal, and economic disempowerment [15]; which, in turn, increases their risk of HIV infection. Research from over a decade in Pretoria has demonstrated that HIV prevalence remained stable among women who engage in sex work at about 68%, but increased among women who do not engage in sex work who use substances, including alcohol, from 34% in 2004–2007 to 47% in 2012–2014 [16]. Furthermore, recent research with women who engage in sex work and women who do not engage in sex work in Pretoria indicated that only 16% of women who were HIV-positive were on ART [17].

Achieving the 90–90-90 goal in South Africa will require reaching vulnerable populations, such as women who engage in sex work and/or substance use, and testing them for HIV, linking them to ART, and retaining them in care. Gender-focused, behavioral interventions that address multiple risk-taking behaviors can facilitate ART initiation and retention. However, contextual and structural factors—such as lack of transportation, food insecurity, myths and beliefs regarding HIV, and navigating the public health system—create barriers that interfere with ART initiation and adherence [18]. Additionally, many vulnerable South African women experience GBV or AOD use (or a combination of these factors), which can contribute to HIV risk [9–12, 19]. Furthermore, multiple barriers exist regarding access to and the use of substance use rehab in South Africa, which is further complicated by the scarcity of affordable programs and a lack of knowledge regarding how to access the limited programs that are available [20].

### Addressing the nexus of substance use, gender-based violence, and HIV risk

Since 2001, our research team has developed and adapted the WHC, an evidence-based, woman-focused, behavioral HIV prevention intervention that reaches high-risk, hard-to-reach women in various contexts. The WHC addresses the intersecting risks of substance use, sex behaviors, and violence and victimization, with the primary goal of increasing skills and knowledge to reduce substance abuse and HIV risks. The original Women’s CoOp intervention was conducted in the United States and was named a Centers for Disease Control and Prevention “best-evidence” behavioral intervention for HIV prevention [21]. Since its inception, it has been adapted from previous iterations to new populations and settings in North Carolina, Rhode Island, Massachusetts, Russia, the Republic of Georgia, and several regions in South Africa [15, 22–27]. To promote the use of EBIs in Africa, the U.S. Agency for International Development (USAID) included the first adaptation of the WHC intervention [22] in its *Compendium of Gender Studies in Africa* [28].

The WHC is grounded in empowerment and feminist theory to emphasize the inverse relationship between substance abuse and personal power and that reduced personal power leads to increased risk behaviors and victimization. Two intervention sessions are held approximately 1 week apart, with each session lasting about 1 h. Sessions can be conducted in groups, workshops, or one-on-one individual sessions. Key elements of the sessions educate participants about the risks of AOD use and how AOD use and sexual risk relate to HIV for women. The WHC also teaches risk-reduction methods such as proper condom use, sexual negotiation, and violence prevention strategies. Women also role-play and rehearse how to use male and female condoms correctly, as well as condom negotiation. At the end of the second session, participants create goals to reduce personal risk. Intervention staff also provide referrals to services and linkages to care.

Following numerous trials in which the WHC demonstrated efficacy, the program was packaged to facilitate widespread dissemination and implementation. The intervention package includes a brief marketing overview for decision-makers and materials for interventionists. It also includes a complete set of intervention materials, the curriculum, and an outreach manual with instructions related to reaching hard-to-reach vulnerable women. Based on the principles of translation frameworks, such as the RE-AIM model [29], the next logical step would be to evaluate the implementation of the packaged WHC in real-world clinical care settings. In this implementation science project, the WHC intervention will be implemented by clinic staff in healthcare clinics and substance use rehab centers as part of standard of care among women living with HIV who use substances. The WHC will address women’s multiple risk-taking behaviors and promote adherence to ART.

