HIV testing is not part of the research because it is performed by clinic staff as part of standard clinic operations. As proof of HIV-positive status, participants must provide a clinic-issued document such as an antiretroviral (ARV) card or ARV medication with identifiable data linking to the participant, or they must consent the research staff to access their hospital records for their results. Viral load is also collected at baseline and 6-month follow-up from the South African National Health Laboratory Service (NHLS) database in the clinics. Viral load testing is also part of the standard of care and the clinics routinely perform HIV viral load testing 6 months after a patient begins taking ART and then 12 months later; however, these intervals may vary by clinic. Viral load test information will be used to validate self-reported ART adherence.

In each cycle, the objective is to enroll 120 women (60 from a HTC/healthcare clinic and 60 from a substance use rehab center) for a sample total of 480, and to follow each enrolled participant at 6 months, with an expected follow-up rate of 90%. At the end of the 6-month follow-up period, we will assess effectiveness of the program using pre-post comparisons to determine whether women reduced their AOD use, are adhering to their ARV regimen, have reduced their sex risk behaviors (e.g., using a condom at every sex act; less transactional sex), and have experienced less to GBV. At the end of each cycle, we will conduct FGDs with a subsample of women who participated in both workshops of the intervention and completed their 6-month follow-up appointment. These study activities will enhance our understanding of women’s satisfaction with the WHC program and suggest modifications to the program for broader acceptability and implementation that will be incorporated into the next cycle.

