To measure the implementation processes and outcomes, we will undertake quantitative data collection with providers and review implementation records to assess fidelity of program implementation. Fidelity checks on a random basis will be conducted on the actual groups conducted. Clinic interventionists and other clinic staff who interact with patients participate in the pre-, mid-, and post-implementation FGDs and also complete the self-administered pre- and post-clinic surveys. We will assess seven implementation outcomes to determine program success, as proposed by Proctor and colleagues [13]. Not all implementation outcomes will be assessed across each of the four cycles; however, the protocol for measuring implementation outcomes will remain constant at each cycle. Some of the intervention outcomes will be measured quantitatively and others will be measured qualitatively. The standard implementation outcomes and their measurement methods are outlined in Table 1.

**Table 1 Tab1:** Standard implementation outcomes and their measurement methods

Implementation outcome	Description	Measurement	Data source	Time point
Appropriateness	The extent to which the WHC^a^ is congruent with the culture of the clinic setting	Focus group discussions	Clinic staff, community women, administrators	Formative
	Organizational Readiness	Texas Christian University organizational readiness for change [46]	Interventionists and administrators	Pre-implementation
	Comprehensive Services Linkage Referrals	Self-report	Participants of the WHC	6-month follow-up
	Comprehensive Services Linkage Referrals	Research staff report	Clinic and research staff	Daily
Acceptability	Feedback on the modified WHC	Focus group discussions	Clinic staff and administrators	Multiple time points from mid- to post-implementation
	Client satisfaction	The Client Satisfaction Questionnaire (CSQ-8) [47]	Participants of the WHC	6-month follow-up
Adoption	Current state of implementation of the WHC and challenges to implementing the WHC	Focus group discussions	Clinic staff	Mid- and post-implementation
Cost	Costs associated with implementing the WHC	Clinic-Patient Contact form [48]	Clinic staff	Throughout the implementation cycle
Feasibility	Exposure to and retention of the WHC	Number of WHC modules being delivered	Clinic staff	Throughout the implementation cycle

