### Analysis

The analysis will treat count outcomes as Poisson distributed. A number of multilevel factors can impact the outcomes, including site/clinics, city, time, and the type of the site (HTC vs. substance use rehab). Because individuals are clustered within sites and sites are clustered within a city, we need to consider the variance inflation factor that results in this clustering. We considered a number of approaches: using random effects, fixed effects, or Generalized Estimating Equations (GEE) considering population-averaged methods. Although a random effects model for sites seems a natural approach, we needed to consider fixed effects of the city and of the site type, which would leave little power left to estimate the random effects distribution. Consequently, we will also use two other methods, GEE and the fixed effects model, to assess sensitivity by comparing the results across these models.

We will use Stata Release 14 (College Station, TX) and SAS version 9.2 (Cary, NC). Data will be examined to determine the extent to which they meet appropriate distributional assumptions. We will use methods described by Ecob and Der to identify outliers in longitudinal models and use methods of case downweighting when extreme cases are identified [40]. Missing data will be handled using multiple imputation methods [41]. The patient-level analyses will be organized into three groups to examine (a) successful reduction of risk behaviors targeted by the WHC (i.e., effectiveness), (b) patient satisfaction, and (c) increasing the number of women receiving ART and adhering to ART, and being admitted to substance use rehab.

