To assess effectiveness, the analysis will compare changes from baseline to 6-month follow-up on the amount of alcohol consumption, biological and self-reported drug use, condom use at last sex, number of sex partners over the past 6 months, and values from scales that measure relationship power and communication. We will start with descriptive analyses, including measures of central tendency, and dispersion (e.g., means, medians, proportions, standard deviations). Bivariate analysis will include paired t-tests, Wilcoxon rank-sum, and tabular statistics and the chi-square test. For multivariable analysis, the xtlogit and xtgee function will be used to specify random effects or fixed effects, and will assume that the correlation matrix is exchangeable. The models will control for other covariates identified in bivariate analyses or hypothesized a priori (e.g., condom use is correlated with substance use). One of the most important covariates in the model will be measures of patient satisfaction. Model performance and fit will be assessed with incremental elimination of variables, likelihood ratio tests, and changes in the Akaike information criterion (AIC) and Bayesian information criterion (BIC) values.

Patient satisfaction analyses will be predominately descriptive to determine if satisfaction improves with each cycle, varies by type of clinic, and by participant characteristics (e.g., alcohol use, pregnancy status).

We assume that the prevalence of patients receiving or adhering to ART or receiving treatment for substance abuse are Poisson distributed and increase from baseline to follow-up. We will use a similar approach outlined in the effectiveness analysis for bivariate and multivariable analyses. Variables considered for multivariable analysis will include patient characteristics, measures of patient success with the WHC, patient satisfaction, and clinic-level characteristics (e.g., type of clinic, provider satisfaction).

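### The WHC is delivered at least partly in groups, but the effectiveness analysis names only site and city as clusters, so workshop correlation arising after baseline would make standard errors too small

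*Protocol article*

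**What the plan says.** **Delivery.** The Background section on substance use, gender-based violence and HIV risk describes two sessions of about one hour, roughly a week apart, and states: "Sessions can be conducted in groups, workshops, or one-on-one individual sessions". Two statements in the Methods concern this study itself. Under Patient-level process and data collection, the end-of-cycle focus groups sample "women who participated in both workshops of the intervention and completed their 6-month follow-up appointment". Under Clinic operations and implementation indicators: "Fidelity checks on a random basis will be conducted on the actual groups conducted".

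**Effectiveness contrast.** Under Patient-level process and data collection: "we will assess effectiveness of the program using pre-post comparisons", from baseline to 6 months.

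**Clustering.** The Analysis section takes up variance inflation on this footing: "Because individuals are clustered within sites and sites are clustered within a city". It weighs random effects for sites, fixed effects and GEE, to be compared as a sensitivity check. It then adds: "Bivariate analysis will include paired t-tests, Wilcoxon rank-sum, and tabular statistics and the chi-square test". The multivariable models, random-effects or fixed-effects logit and GEE, "will assume that the correlation matrix is exchangeable". No workshop, group or interventionist level, robust variance or ICC is named.

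**The concern.** Women who attend the same workshop share a session, peers, role-play and discussion, so their later outcomes may be alike for reasons unconnected with site. This likeness arises after the baseline visit and so enters the 6-month measurement only.

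That timing matters for a before-after analysis. A site effect common to both visits drops out of the change. So does a woman's own level, and a woman-level intercept cannot link different women in any case. A workshop effect present only at follow-up stays in the change and is shared by several women. The paired t-test treats the women's changes as independent. An exchangeable correlation by woman or by site, with no robust variance, does not represent correlation among some women at one visit only.

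At stake are the width of the intervals and the false-positive rate of the effectiveness tests for women treated in groups.

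**Working it through.** **The plan's own figures.** The Power section prints detectable differences of 4 points (mean adherence 87%, SD 17.28) and 13 points (from 56% or 55%). Alpha, ICC and number of periods are not stated. The Hussey-Hughes variance with 4 clusters, 4 steps, 5 periods, 240/5 = 48 observations per cluster-period, two-sided 5% alpha (assumed) and ICC 0 gives 4.42 points, 12.7% and 12.7%, which round to the printed values. An ICC of 0.01 gives 5.19, 14.9% and 14.9%, which do not. The match is not unique, because a large ICC between 0.2 and 0.5 would also fit.

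**Inputs for the check**
- From the article: 480 women, 90% followed, so 0.90 × 480 = 432; 8 sites, so 432/8 = 54 followed women per site.
- Assumed: m followed study women per workshop; ICC, the workshop share of the 6-month variance; rho, the correlation between a woman's two visits; two-sided 5% tests.

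**Formula.** With variance σ² at each visit, a woman's change has variance 2σ²(1 − rho). Two women in one workshop share covariance ICC × σ² in their changes, so the ICC of the change is ICC / [2(1 − rho)]. Then:
- design effect DE = 1 + (m − 1) × ICC / [2(1 − rho)]
- true SE / reported SE = √DE
- type I error = 2 × [1 − Φ(1.96/√DE)]

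**Results at rho = 0.5**

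| m | ICC | DE | SE ratio | Type I error |
|---|---|---|---|---|
| 5 | 0.01 | 1 + 4 × 0.01 = 1.04 | 1.02 | 5.5% |
| 8 | 0.05 | 1 + 7 × 0.05 = 1.35 | 1.16 | 9.2% |
| 10 | 0.05 | 1 + 9 × 0.05 = 1.45 | 1.20 | 10.4% |
| 15 | 0.10 | 1 + 14 × 0.10 = 2.40 | 1.55 | 20.6% |

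**Sensitivity to rho.** At m = 8 and ICC 0.05, rho of 0.3, 0.5 and 0.7 gives DE 1.25, 1.35 and 1.58, with type I error 8.0%, 9.2% and 11.9%. The direction does not change.

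**Simulation** (8 sites × 6 workshops × 9 women = 432, rho 0.5). At ICC 0.05 the true SE is 0.0572 SD units against 0.0481 when workshops are ignored, a ratio of 1.19; the formula gives √1.40 = 1.18. Type I error is 10.0%, and it is 7.2% at ICC 0.02 and 14.7% at ICC 0.10.

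**Remedies in the same simulation** (ICC 0.05)
- Site-clustered sandwich SE, 8 sites, uncorrected: SE 0.0514, type I error 11.0%.
- Site-clustered SE, small-sample correction, t on 7 df: 4.9%.
- Workshop-level analysis: 5.2%.

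**Do the printed detectable differences suffer?** For a paired change at rho 0.5 with 432 women:
- Mean: SE = 17.28 × √(1/432) = 0.83; × 2.80 = 2.3 points. At the largest ratio, 2.33 × 1.55 = 3.6, below 4.
- Proportion: SE = √(0.56 × 0.44/432) = 0.0239; × 2.80 = 6.7 points. At the largest ratio, 6.7 × 1.55 = 10.4, below 13.

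**The case against.** **The article is condensed.** Its list of multilevel factors is open-ended, and the section on implementing the WHC names the provider among the nested levels to be considered, so a workshop term might stand in a fuller document. This has some force. But the Analysis section does more than stay silent: it sets out a hierarchy, chooses models on that basis, and leaves out the level at which group sessions take place.

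**The share of group delivery is unknown.** The Background sentence allows one-on-one sessions, for which there is no inflation. This stands. The two Methods statements establish some group delivery, but not how much.

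**The size may be negligible.** Sessions are also offered to clinic patients outside the study, so study women per group may be few. Women may attend one session only, or different groups. The dose is two hours and the outcome is at 6 months. Women recruited together may already be alike at baseline, and that part can cancel. All this stands; it is why the range starts at a 2% error in the SE.

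Three stronger readings are tempting and should not be drawn:
- *Each workshop is led by one interventionist.* The article never gives the number of staff per group. The argument needs only a shared session and peers.
- *The 4- and 13-point detectable differences are understated.* Those figures come from a stepped-wedge formula, and a design effect for a paired change cannot be applied to them. The paired detectable differences stay below the printed values even at the largest ratio.
- *Every before-after test must be anticonservative.* Workshops lie within sites, so a site-clustered variance with a small-sample correction would hold the error rate. The article considers GEE but states no such variance.

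**Conclusion.** The point holds in limited form. Followed as written, the plan gives standard errors that are too small for group-delivered women whenever workshop correlation arising after baseline is above zero. The direction follows from the design. The size does not come from the documents: with 5 to 15 study women per workshop, ICC 0.01 to 0.10 and between-visit correlation 0.5, all assumed, the true SE is about 1.02 to 1.55 times the reported one and the type I error about 5.5% to 21%. A middle case of 9 or 10 women and ICC 0.05 gives about 10%. The finding concerns the intervals and tests of the effectiveness analysis; it does not reach the printed detectable differences.

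**What to change.** Record for each woman the workshop she attended (by first session, with date and interventionist) and whether delivery was group or one-on-one. In the effectiveness models, specify one of the following:

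1. a workshop random effect acting at the 6-month visit only, with one-on-one women and non-attenders as singletons;
2. standard errors clustered on workshop, with site as a fixed effect;
3. standard errors clustered on site, with a small-sample correction and a t reference on 7 degrees of freedom.

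Keep the paired t-test as a description only, and take inference on the change from the chosen model.

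The cost is one extra identifier on the session record, one model term or variance option, and somewhat wider intervals. The identifier should be captured at delivery, since it may be hard to recover later. Option 3 needs no identifier and remains available for cycles already completed.
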